### Handling missing data

Over the period covered by this study (2013–2018), there have been changes in the number of practices and CCGs in England. Some practices have closed, new practices opened and some CCGs merged over the period; as such, we will have missing values for some observations. To maximise the use of existing observations, we will retain all observed values in the main analysis and impute the missing values using multiple approaches.^40^ Missing values for the period before a new CCG was formed through merger of pre-existing CCGs will be imputed using the mean value of the CCGs that constitutes the merger; subsequently, these closed CCGs will be dropped from the dataset. Other missing values in this study will be handled using multiple imputation method on Mplus V.8.2. We will run a separate imputation model for the practice and CCG level datasets, the results will be averaged across 20 imputed datasets. Complete case analysis will be conducted as part of the sensitivity analyses for this study to examine the consistency of the results from the imputed set.

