### Statistical analysis

Our first analysis will be an interrupted time series to investigate whether antibiotic prescribing rate in England has changed over time, and how such changes, if any, are associated with the QP implementation in March 2015. This will be conducted using the ordinary least square regression method^41^ to assess whether the 2015/2016 QP establishment resulted in a shift in the level and trend in antibiotic prescribing in primary care in England compared with the period before the intervention. Using the practice-level dataset, a univariate time series with the mean antibiotic items (STAR-PU weighted) prescribed in all primary care practices in England for each month will be conducted using the *ITSA* function on Stata, with post-trend specification to show a postintervention trend. The Cumby-Huizinga general test for autocorrelation will be used for general specification test of serial correlation in the time series data.^42^

A new QP guideline was implemented each financial year with changes in the prescribing rate target and the proportion that improved prescribing constituted in the QP award for each year. Our mediation analyses will investigate the effects of the QP by comparing antibiotic prescribing rate in the financial year before its implementation to each subsequent year postimplementation; as such, our dataset for the mediation analyses will have the control group as the financial year before QP and the intervention group as a specific post-QP implementation year. Three analyses will be conducted for each of the three financial years since QP establishment. This will enable us to compare the effects of the different target levels that have been set over the years and the proportions of the QP award attributed to improvement in antibiotic prescribing.

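### Months when a practice did not exist are treated as missing and multiply imputed, and a merged CCG's earlier rate is set to a mean with no stated weight

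*Protocol article*

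**What the plan says.** Under Handling missing data, the protocol gives structural change as the reason for missingness: "Some practices have closed, new practices opened and some CCGs merged over the period; as such, we will have missing values for some observations". It then states that "we will retain all observed values in the main analysis and impute the missing values using multiple approaches", so the imputed data form the main analysis.

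Two rules follow.

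- **Mergers.** Values for the period before a merged CCG existed are "imputed using the mean value of the CCGs that constitutes the merger". The constituents are then removed: "subsequently, these closed CCGs will be dropped from the dataset".
- **Everything else.** "Other missing values in this study will be handled using multiple imputation method on Mplus V.8.2". This applies at both levels: "We will run a separate imputation model for the practice and CCG level datasets, the results will be averaged across 20 imputed datasets".

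No rule exempts months in which a practice was closed or not yet open. The one stated check is that "Complete case analysis will be conducted as part of the sensitivity analyses".

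Under Statistical analysis, the practice dataset feeds the interrupted time series as "a univariate time series with the mean antibiotic items (STAR-PU weighted) prescribed in all primary care practices in England for each month". Under Variables, the primary outcome is a monthly rate of items per STAR-PU at CCG level. Under Data sources, the practice denominator is built from that month's registered patients by age and sex, and the 2013 to 2015 CCG data are to be derived from practice data.

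**The concern.** A practice that has closed or has not yet opened has no prescribing and no registered patients, so its STAR-PU denominator is undefined. There is no unobserved true value for an imputation model to recover. Because closures and openings are named as causes of missingness and the merger rule does not cover them, the plan as written gives these practices imputed rates in the main analysis.

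These imputed values are not spread evenly over calendar time. Practices that opened during the study are filled in early, and practices that closed are filled in late. If either group's imputed rates differ from those of operating practices, the artefact changes with time. The segmented regression can then read it as a change in level or slope, which is what it is meant to estimate.

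The merger rule raises a separate and smaller issue. The outcome is a ratio, so the rate of two CCGs combined is their total items over their total STAR-PUs. A simple mean equals that only when the CCGs match in size or in rate. Where a merger falls between the pre-QP year and the comparison year, an averaged baseline is set against a genuinely pooled follow-up, which produces a spurious change for that CCG.

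**Working it through.** The protocol gives no error figure on this point, so there is none to reproduce. It also gives no counts of closures, openings or mergers, no CCG sizes and no rate gaps. Those inputs are assumed below and shown as ranges.

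**Inputs from the protocol.** England mean 2013/14: 1.61 items per STAR-PU. Targets: reductions of 1% (0.01 x 1.61 = 0.016) and 4% (0.04 x 1.61 = 0.064). CCGs: 209, of which 187 took part in the survey that supplies mediators.

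**1. Practices that did not exist.** Let s be the share of practices in a month's mean that are imputed, and d the relative gap between their imputed rates and the mean m of operating practices. The monthly mean becomes (1 - s)m + s·m(1 + d) = m(1 + s·d), a relative shift of s·d.

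| s (assumed) | d (assumed) | Shift in monthly mean |
|---|---|---|
| 2% | 5% | 0.1% |
| 5% | 10% | 0.5% |
| 10% | 20% | 2.0% |
| 15% | 20% | 3.0% |
| any | 0 | 0 |

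At the start of the series the imputed practices are all later openers; at the end they are all earlier closers. So s and d vary over time, and the shift is not a constant that an intercept would absorb.

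**2. Merged CCGs.** Let two CCGs have rates r1 and r2, and let w be the first one's share of STAR-PUs. The simple mean is (r1 + r2)/2 and the pooled rate is w·r1 + (1 - w)·r2. The difference is (0.5 - w)(r1 - r2), of size (larger share - 0.5) x rate gap.

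| Size ratio (assumed) | Gap (assumed) | Error, as % of the two CCGs' mean rate |
|---|---|---|
| 1:1 | any | 0 |
| 2:1 | 10% | (0.667 - 0.5) x 10% = 1.7% |
| 2:1 | 20% | 3.3% |
| 3:1 | 10% | 2.5% |
| 3:1 | 20% | 5.0% |

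The sign depends on whether the larger CCG has the lower or the higher rate. At a mean of 1.61, an error of 1.7% is about 0.027 items per STAR-PU, larger than the 0.016 first-year target, so it could change whether that one CCG counts as having met its target.

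**3. Dilution in the overall estimate.** If 10 or 20 of 209 CCGs were affected (assumed), each by 2.5% and all in the same direction, the average over CCGs would move by 10/209 x 2.5% = 0.12% or 20/209 x 2.5% = 0.24%. Errors of opposite sign would reduce this.

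**The case against.** The best defence has three parts.

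- The text does not say the merger mean is unweighted. That is only its plain reading, and if STAR-PU weighting was meant, one phrase settles the matter. The boundaries used to map the 2013 to 2015 practice data are also unstated; if they are the later ones, the pre-QP outcome for merged CCGs may already be correct. This stands as a reason to clarify, but a rule for a ratio outcome should name its weight.
- A complete case analysis is planned. It may expose the practice problem, but it is only a sensitivity analysis and does not clearly undo the merger averaging.
- The error sizes rest on assumptions. This stands in full.

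A reader might also infer more than the protocol supports.

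- *That merger averaging biases the time-series level and trend.* It does not: that series is built from the practice dataset, and the merger rule acts on CCGs.
- *That 1.7% to 5.0% is the error in a study result.* It is the assumed error in one merged CCG.
- *That averaging would halve the number of GPs.* The protocol defines that covariate per practice, so a mean does not halve it.
- *That imputed practices double-count patients.* An equal-weight mean of rates sums no populations; what changes is the mix of practices.
- *That an equal-weight mean of practice rates is itself an error.* This is largely a choice of estimand.

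**Conclusion.** The concern holds on two separate points of unequal weight.

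The firmer one is the practice rule. As written, the main analysis imputes rates for months in which practices did not exist and carries them into the monthly mean behind the interrupted time series. The possible distortion is 0.1% to 3.0% of that mean if 2% to 15% of practice-months are imputed and rates differ by 5% to 20%. It is zero if imputed and operating practices have the same rates, though non-existent units would still be in the data.

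The second is the merger rule. Read as a simple mean, it misstates a merged CCG's pre-merger rate whenever the constituents differ in both size and rate. It reaches only merged CCGs, and only the CCG-level mediation and binary target analyses. It largely cancels where both compared years precede the merger, and its effect on the overall estimate is likely much smaller than the single-CCG figures. The number of mergers and closures is not given, so neither effect can be sized more closely.

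**What to change.** 1. State that months before a practice opens or after it closes are not applicable and are not imputed, so that each month's mean uses only practices open in that month.
2. Replace the merger mean with total items over total STAR-PUs of the constituent CCGs, for example by mapping practice data to the later boundaries. The practice data are already being obtained, and a practice-to-CCG mapping is already planned for the early years.
3. Restrict multiple imputation to values truly unobserved in units that existed, such as mediators for the 22 CCGs (209 - 187) without survey data.

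The cost is a change of wording and minor extra data preparation. No new data source is needed.

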### Statistical analysis

Our first analysis will be an interrupted time series to investigate whether antibiotic prescribing rate in England has changed over time, and how such changes, if any, are associated with the QP implementation in March 2015. This will be conducted using the ordinary least square regression method^41^ to assess whether the 2015/2016 QP establishment resulted in a shift in the level and trend in antibiotic prescribing in primary care in England compared with the period before the intervention. Using the practice-level dataset, a univariate time series with the mean antibiotic items (STAR-PU weighted) prescribed in all primary care practices in England for each month will be conducted using the *ITSA* function on Stata, with post-trend specification to show a postintervention trend. The Cumby-Huizinga general test for autocorrelation will be used for general specification test of serial correlation in the time series data.^42^

A new QP guideline was implemented each financial year with changes in the prescribing rate target and the proportion that improved prescribing constituted in the QP award for each year. Our mediation analyses will investigate the effects of the QP by comparing antibiotic prescribing rate in the financial year before its implementation to each subsequent year postimplementation; as such, our dataset for the mediation analyses will have the control group as the financial year before QP and the intervention group as a specific post-QP implementation year. Three analyses will be conducted for each of the three financial years since QP establishment. This will enable us to compare the effects of the different target levels that have been set over the years and the proportions of the QP award attributed to improvement in antibiotic prescribing.

Using a unified model for the natural direct and indirect effects,^31^ we will investigate the relationship between the QP initiative, the potential mediators and antibiotic prescribing rate with adjustment for the practice and CCG characteristics. This approach addresses the issues associated with the traditional approach to mediation analysis that obtains natural direct and indirect effect estimates through a non-trivial combination of parameter estimates from multiple models for the regression of the mediator and that of the outcome.^32 43^ Also, the unified model is applicable to nonlinear regressions, different measurement types for outcome and mediator variables, and allows for interaction between the exposure and the mediator.^31^

We will first fit single-mediator models with each mediator separately modelled using the *medeff* function in Stata.^44^ With the single-mediator models, we will be able to establish the individual influence of each potential-mediator variable. Variables that showed a mediating effect in the single-mediator models will be added to build a multiple-mediator model using a sequential mediation analysis method.^45^

A sequential multiple-mediator analysis is preferred to merely summing the effects of the single mediators because the sum may differ from the joint mediated effect, particularly as our potential mediators may influence one another.^45^ Modelling all the significant mediators together provides a more accurate assessment of the mediation effects and causal relationship,^46 47^ while assessing the indirect effect of a group of mediators in explaining how and why the intervention impacts on the outcome. The ordering of the mediators in the sequential mediation analysis will be based on evidence from the literature and the outcome of our stakeholders’ workshop designed to identify possible pathways between the predictor, mediators and outcome. The workshop that will validate our conceptual model will also enable us to identify what mediators affect one another and inform interactions to include in our model. All analysis will be conducted in the Stata statistical package V.15.1.

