**Figure 1 F1:**
[figure not shown]
Conceptual model. The direct effect is represented by the path between the QP initiative (predictor) and antibiotic prescribing rate (outcome). *Not directly observed within our data. AMS, antimicrobial stewardship; CCG, Clinical Commissioning Group; CMO, Chief Medical Officer; QP, Quality Premium; TARGET, Treat Antibiotics Responsibly, Guidance, Education, Tools.

Our conceptual model suggests that in addition to its direct impact, the QP initiative acts by stimulating and enhancing the adoption of existing strategies to reduce and optimise antibiotic prescribing. In investigating the potential pathways connecting QP to reductions in antibiotic prescribing, we will be examining the hypothesis that factors like the Chief Medical Officer’s (CMO) letter, Treat Antibiotics Responsibly, Guidance, Education, Tools (TARGET) toolkit, antibiotic auditing, benchmarking, local incentives at CCG level, prescribers and patients’ antimicrobial stewardship (AMS) education/training can transmit part of the influence of the QP initiative to antibiotic prescribing.

First implemented in September 2014, the CMO letter, which provided social norm feedback to primary care practitioners in England whose antibiotic prescribing rate was in the top 20%, reduced antibiotic prescribing by 3.3% in 6 months in a randomised trial.^26^ The criteria for selecting practices that received the letters in the subsequent years changed with the addition of measures like a change in antibiotic prescribing over time and whether practices have previously been sent CMO letter.

Another important mediator hypothesised in our conceptual model is AMS education/training of prescribers and patients. Educating and training prescribers on the importance of antibiotic stewardship and ways to promote prudence can help prescribers make better decisions on when an antibiotic is indicated and can also improve patients’ knowledge on the appropriate use of antibiotics. AMS interventions targeted at patients can improve their knowledge of when antibiotics are not needed and increase confidence and skills on how to self-care, which can result in reduced consultations for self-limiting illness and thus reduced antibiotic prescriptions.

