### Data sources

The study will constitute secondary analyses of antibiotic prescribing data from NHS England covering the period 2013 to 2018. CCGs were established in England in April 2013 following the Health and Social Care Act 2012.^33^ Data on antibiotic prescribing in primary care at CCG level will be sourced from the NHS England Antibiotic Quality Premium Monitoring Dashboard, which is produced by the NHS Business Services Authority (BSA).^34^ Primary Care prescribing data are publicly available from the NHS BSA website. The dataset contains the number of antibiotic items (STAR-PU) prescribed in each CCG from the financial year 2015/2016 to 2018/2019, with data for October 2018 the latest at the time of this protocol. Data for the period 2013 to 2015 will be mapped to CCG level from the practice-level data.

Practice-level antibiotic prescribing data will be sourced from OpenPrescribing, an Evidence-Based Medicine DataLab project by the University of Oxford. OpenPrescribing publishes monthly antibiotics prescribing data from August 2013, with data for October 2018 the latest at the time of this protocol. Practice-level antibiotic prescribing data from OpenPrescribing is not STAR-PU weighted, so the extracted data will be STAR-PU weighted using figures from the 2013 Item-based age–sex weighting for oral antibacterials^14^ and the number of registered patients in each age–gender category in a practice for each specific month.

Overall, the dataset offers coverage of at least 3 years postintervention given that antibiotic prescribing became a QP priority in March 2015. This will be important in investigating the immediate direct and indirect effects of the QP initiative while giving an insight into the sustainability of the identified effects (if any) in the long-term.

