### Variables

The predictor will be a binary variable indicating the implementation of the QP intervention. The intervention will include all periods after March 2015 when the 2015/2016 QP guidance in England was published, while the control will be periods prior to this. The primary outcome of interest is the rates of antibiotic prescribing at CCG level in England, which will be a continuous variable indicating the number of items (per STAR-PU) prescribed per month.

To account for differences in practice and CCG characteristics that can contribute to variance in antibiotic prescribing, we will be adjusting for the number of general practitioners in each practice (from the NHS Workforce data),^35^ the index of multiple deprivation (from the Department for Communities and Local Government),^36^ prevalence of comorbidities (asthma, chronic obstructive pulmonary disease, diabetes, cancer, chronic kidney disease (from the NHS Quality and Outcomes Framework database)),^37^ the prescribing rate of other non-antibiotic drugs (opioids and benzodiazepines) and seasonal influenza vaccination rate (from PHE).^38^

Mediator variables will be derived from the questionnaire data from a PHE survey,^39^ with 187 of the 209 AMS leads representing CCGs in England and data from other organisations that have evaluated the interventions treated as potential mediators in this study. In the PHE survey, participants were required to complete questionnaire items, which included their adoption of national and local strategies in their respective CCG to enable them to meet QP targets on antibiotic prescribing in primary care. The mediator variables will be binary or continuous variables, indicating the adoption of key interventions and intermediaries that are hypothesised to reflect in the integration of the QP guidance in improving antibiotic prescribing in primary care practices.

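### The pre-QP line of the interrupted time series contains the first CMO letter with no term for it, which alone biases the QP trend change by about +0.13 to +0.54% a year

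*Protocol article*

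**What the plan says.** Under Statistical analysis, the protocol article plans "a univariate time series with the mean antibiotic items (STAR-PU weighted) prescribed in all primary care practices in England for each month". It is fitted by ordinary least squares with one interruption, at the QP implementation in March 2015. The aim is to detect "a shift in the level and trend in antibiotic prescribing in primary care in England compared with the period before the intervention", and a post-intervention trend is also to be shown.

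Under Data sources: "OpenPrescribing publishes monthly antibiotics prescribing data from August 2013, with data for October 2018 the latest at the time of this protocol". Under Variables: "The intervention will include all periods after March 2015".

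The text on the conceptual model in the Introduction dates the letter: "First implemented in September 2014, the CMO letter". It went to practitioners "whose antibiotic prescribing rate was in the top 20" per cent, and it "reduced antibiotic prescribing by 3.3% in 6 months in a randomised trial". The same paragraph says that letters were also sent in later years, under changed selection criteria.

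No letter term, second interruption or exclusion is described for the time series. Under Sensitivity analyses, the dummy implementation dates move by 1 to 3 months either side of publication. September 2014 is 6 months before March 2015, so they do not reach it.

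**The concern.** A level-and-trend model judges QP against a straight line fitted to the pre-QP months and carried forward. A drop near the end of a short baseline is read partly as a steeper downward trend. If that drop came from another intervention, the carried-forward line falls too fast and the trend change comes out too high. The article itself names such an intervention and gives its size.

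The trend change is one of the two quantities that the time series is meant to test. A real QP decline in trend could look smaller than it is, or like no change.

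**Working it through.** **Window (the article's only stated figure here).** Post-QP: April 2015 to October 2018 = 9 + 12 + 12 + 10 = 43 months, or 3.6 years. This agrees with the stated coverage of at least 3 years. Pre-QP: August 2013 to March 2015 = 5 + 12 + 3 = 20 months. If March 2015 is itself counted as a QP month, the split is 19 and 44. With August 2013 as month 1, September 2014 is month 14 and October 2018 is month 63.

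**Size of the letter effect on the national mean, s.** Full: 0.20 x 3.3% = 0.66%. Half: 0.10 x 3.3% = 0.33%. The share lettered is an assumption, because the article does not state the allocation. Taking the top 20% of prescribers as 20% of the mean is another. All results scale in proportion to s.

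**Pre-QP fit with zero QP effect (20 months, step from month 14).**
- Mean month 10.5; sum of squares = 20 x (400 - 1)/12 = 665.
- Cross-product = 7 x (17 - 10.5) = 45.5. Slope per unit of s = 45.5/665 = 0.0684 a month, downward.
- False trend change at s = 0.66%: 0.0684 x 0.66 x 12 = +0.54% a year.
- Line at month 63, per unit of s: 7/20 + 0.0684 x (63 - 10.5) = 3.94 below baseline. If the effect persists, the true series is 1 below baseline, so the apparent effect is (3.94 - 1) x 0.66 = +1.94%. If it has faded, 3.94 x 0.66 = +2.60%.

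**All variants** (each range is s = 0.33% to 0.66%; the level change is for a persisting effect at s = 0.66%):

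| Pre-QP months | Start | Shape | Slope per unit s | Trend change, % a year | Oct 2018, persists, % | Oct 2018, faded by QP start, % | Level change, % |
|---|---|---|---|---|---|---|---|
| 20 | Sep | step | 0.0684 | 0.27-0.54 | 0.97-1.94 | 1.30-2.60 | +0.05 |
| 20 | Oct | step | 0.0632 | 0.25-0.50 | 0.86-1.73 | 1.19-2.39 | -0.02 |
| 20 | Sep | 6-month ramp | 0.0503 | 0.20-0.40 | 0.61-1.23 | 0.94-1.89 | -0.16 |
| 20 | Oct | 6-month ramp | 0.0412 | 0.16-0.33 | 0.44-0.88 | 0.77-1.54 | -0.26 |
| 19 | Sep | step | 0.0684 | 0.27-0.54 | 0.97-1.94 | 1.30-2.60 | 0.00 |
| 19 | Oct | step | 0.0614 | 0.24-0.49 | 0.83-1.66 | 1.16-2.32 | -0.08 |
| 19 | Sep | 6-month ramp | 0.0450 | 0.18-0.36 | 0.52-1.04 | 0.85-1.70 | -0.24 |
| 19 | Oct | 6-month ramp | 0.0336 | 0.13-0.27 | 0.30-0.60 | 0.63-1.26 | -0.35 |

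The trend-change bias is positive in every row. With a persisting effect the fitted post-QP trend is exactly unbiased. The level change is within about 0.1% for a persisting step. For a ramp it shows a small false drop, and for a faded step at s = 0.66% with 20 pre-QP months it is biased by about +0.6 to +0.7%.

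**Later letters.** No effect size is given for these. Suppose three yearly letters in the post-QP period each add a persisting step of the same size as the first (September step, 20 pre-QP months), and none is credited to QP. With the later letters placed in October, the October 2018 figure is -0.16% at s = 0.33% and -0.32% at s = 0.66%. Placed in November it is -0.15% and -0.29%. If later letters add only 0.33% each against a first step of 0.66%, it is +0.81%.

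**The case against.** **The size depends on assumptions.** This stands. The share lettered, the shape and the persistence are not in the article. A randomised trial suggests that not every top-20% practice was lettered at first. A reader might infer that the plan hides 0.9-1.9% of the QP effect by October 2018. That needs an instant, persisting step; a ramp gives less.

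**October 2018 is not a stated estimand.** This also stands. The plan names level change, trend change and post-intervention trend. The remark on sustainability under Data sources concerns direct and indirect effects. Those belong to the mediation analyses, which compare financial years and use no extrapolated line. The trend change is still a stated target.

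**The net sign is open.** This stands if later letters are kept apart from QP. On the article's conceptual model the letter is a mediator, so later letters would count as QP effect. The first letter preceded QP and cannot be credited to it.

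**Noise and seasonality may matter more.** The standard error of the October 2018 contrast is 2.07 times the monthly residual SD, so 2.07% at an assumed SD of 1%. An assumed 5% winter cosine left unmodelled would move that contrast by about -3.6 to -8.2%. Both are fair context, but neither removes the bias.

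**A low-prescriber subgroup is planned.** It helps only in part. It covers the bottom 20% and is classified at March 2015, after the letter.

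**Conclusion.** The point holds in a limited form. A known co-intervention sits in the last 7 of 20 pre-QP months, is not modelled, and is not reached by the date sensitivity analyses. Taken alone it biases the trend change upward by about 0.13 to 0.54% a year, assuming that half or all of the top 20% were lettered. Measured against the extrapolated line, this is 0.3-1.9% at October 2018 if the effect persists, and up to 2.6% if it fades by QP start.

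That is comparable with the 1% target in the 2015/2016 guidance. A reader might infer that it also rivals the 4% target or invalidates the whole time series. The figures support neither: no variant above exceeds 2.6%, the post-QP trend is unbiased for a persisting effect, and the level change is nearly so for a persisting step. Nor is it established that the net result understates QP once later letters are considered. The time series is also a first step in a study whose aim is mediation.

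**What to change.** Keep the planned model as the main fit. Under Sensitivity analyses, pre-specify two refits and report the level and trend change from each:

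- **Offset.** Enter the first letter's effect from September 2014 as a fixed offset at zero, half and full size. Full size is 3.3% times the share of national items from top-20% practices, which the practice-level data give. Fit each as a step and as a 6-month ramp, both persisting and fading by March 2015.
- **Practices outside the top 20%.** Refit on these alone. Classify them on prescribing before September 2014, using a mean of several months to limit regression to the mean.

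A free step term from September 2014 should be a secondary check only. Report the trend change as conditional on these results, and state whether later letters count as part of the QP effect.

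The cost is a few extra fits on data already held. The offset treats an uncertain trial estimate as known, which is why several sizes and shapes are needed. With 20 pre-QP months, a free step term multiplies the standard error of the trend change by 1.60 to 1.72, a rise of about 60-70%.
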